## Abstract

**Background:**

Healthy movement behaviors in early childhood are believed to track to adulthood, potentially imparting protective benefits against non-communicable diseases. Highlighting the collaborative and complementary roles of parents and educators in promoting health of young children, this study aims to enable parents and teachers to successfully promote healthy movement behaviors in young children. Guidelines for physical activity, sedentary screen time, and sleep of children aged 2 to 6 years will be systematically disseminated to parents and teachers of children enrolled in early childhood education centers (ECECs) in Hong Kong. An evaluation will be conducted to assess the implementation process and the outcomes of the dissemination of said guidelines.

**Methods:**

The evaluation will include formative and summative components to examine the implementation (i.e., process evaluation) and the outcomes (i.e., outcome evaluation). Participants include teachers, parents, and children from ECECs in Hong Kong. The process evaluation will be guided by the RE-AIM framework (i.e., reach, efficacy, adaptation, implementation, maintenance). Data gathering and analysis will take a mixed-methods triangulation design - convergence model. The outcome evaluation consists of a non-randomized observational study, using quantitative data from questionnaires and accelerometers. The primary outcome to be measured is the extent to which children meet the guidelines for physical activity, sedentary screen time, and sleep; the secondary outcome is teachers’ and parents’ knowledge and awareness of the guidelines.

**Discussion:**

Young children who engage in healthy movement behaviors are likely to become adults who will have the disposition to engage in behaviors that have protective effects against non-communicable diseases. The findings of this evaluation are expected to contribute to improving the strategies of systems and government agencies that aspire to promote healthy movement behaviors of young children.

## Background

In recent years, a worldwide push for promoting physical activity participation across populations has ramped up. Physical activity promotion has been shown to be of critical importance, with conclusive evidence showing physical inactivity as one of the leading risk factors for death worldwide – 3.3 million deaths per year – and a major risk factor for non-communicable diseases (NCDs) [1]. The most recent comprehensive estimate revealed that the global cost of physical inactivity to health care systems was INT$53.8 billion in the year of 2013 (INT$1 would buy in a cited country a comparable amount of goods and services that US$1 would buy in the United States) [2]. Furthermore, physical inactivity-related deaths indirectly cost INT$13.7 billion (lost productivity), and accounted for 13.4 million disability-adjusted life years (DALYs) worldwide. As such, investments to promote physical activity are warranted more than ever. Recently, the World Health Organization (WHO) released the *2020 Guidelines on physical activity and sedentary behavior* [3], which targets children aged five years and above, adolescents, adults, older adults, and specific groups that include pregnant and postpartum women, and people living with chronic conditions or disability. A year prior, the *WHO Guidelines on physical activity, sedentary behavior and sleep for children under 5 years of age* [4] was launched*.*

The guidelines for children under 5 years of age have been developed not only to mitigate physical inactivity, but also to respond to concerns related to whole-day movement behaviors (i.e., 24-h movement guidelines). From earlier work that developed similar guidelines for young children in Canada and Australia, it was established that desirable movement behaviors of young children consist not only of greater physical activity, but also of less sedentary screen time, and longer sleep [5–7]. It was further highlighted that in the early years, balanced movement behaviors gain benefits in motor and cognitive development; cardiometabolic, skeletal, and psychosocial health; and reduced risks for adiposity and injuries. These benefits exceed potential harm [8] and the movement guidelines have been gaining momentum across the globe [9]. A recent systematic review showed evidence that meeting the 24-h movement guidelines was associated with better health-related quality of life including the social-cognitive, behavioral, and emotional domains in preschool-aged children [10], indicating wider associated benefits for health.

### Movement behaviors of young children in Hong Kong

In Hong Kong, the WHO guidelines for children aged under 5 years had been adopted by the Centre for Health Protection (CHP), with the target age group modified to include 2 to 6 years old [11]. This modification reflects the age of children when they typically attend pre-primary school (i.e., early childhood education center [ECEC] which consists of nursery and kindergarten in Hong Kong). Enrollment in ECEC is not mandatory for children in Hong Kong. However, the local Education Bureau notes that virtually all children aged 3 to 5 years old attend kindergartens, based on the data recorded in the 2019/20 school year [12]. The guidelines that were adopted by the CHP are currently being disseminated through ECECs who have volunteered to join a public health campaign that promotes healthy eating and physical activity for pre-primary school-aged children in school and home settings [13]. The ongoing public health campaign has a wider focus on the physical health of young children, and implementation of the movement guidelines has yet to be systematically examined. A deliberate and strategic implementation plan and evaluation are crucially important because key information from movement guidelines for young children need to be distilled and packaged to ensure effective dissemination to stakeholders [14].

Hong Kong has a rapidly ageing population, where adults aged 65 years old and above are expected to make up as much as 33% of the population in 2039 and 38% of the population in 2069 [15]. Thus, getting children towards a path of healthy movement behaviors early is an important contributor to managing a future super-aged society. Research has shown that childhood activity patterns track to adulthood [16], and active adults in the future would contribute to mitigating the health care burden of a super-aged population. However, it appears that further work is needed to achieve this. The most recent survey by the Hong Kong Department of Health on the physical activity of pre-primary school children revealed that less than 30% achieved the recommended 180 min of daily physical activity [17]. Moreover, only 15% of parents were aware of the physical activity recommendations for children aged 2 to 6 years. In contrast, recommendations on sedentary screen time appears to be better applied as the children’s median screen time was reported to be 60 min, and 79% of parents were aware of the screen time recommendations for young children. There has been no information thus far on the sleep patterns of young children.

While the health authorities in Hong Kong have adopted the WHO-recommended movement guidelines for young children, there is currently limited knowledge of the uptake of these movement behaviors in home and school settings. There is clearly a need to promote healthy movement behaviors in young children through mechanisms that involve the adults that they interact with (e.g., parents, teachers). Thus, a systematic and deliberate approach to empower parents and teachers by enhancing their knowledge and understanding of healthy movement behaviors is crucial.

### The current study

The current strategies that are in place to promote healthy movement behaviors of young children in Hong Kong could be enhanced by leveraging the collaborative and complementary roles of parents and educators. In this current study, we aim to enable parents and teachers, so that they may successfully promote healthy movement behaviors in pre-primary school-aged children. The movement guidelines for children aged 2 to 6 years, which have been issued by the CHP will be systematically disseminated to parents and teachers of children enrolled in ECECs in Hong Kong. The dissemination plan will be informed by active engagement with stakeholders through formative work. An evaluation will be conducted to assess the implementation process and the outcomes of the dissemination. Specifically, the evaluation will: (1) assess the uptake of the dissemination of the movement guidelines by parents and teachers of children in ECECs, (2) identify the barriers and enablers to implementation of the movement guidelines in the local context, and (3) evaluate the impact of the school-based dissemination on parents, teachers, and children.

## Materials and methods

### Dissemination plan

Public health strategies will be successful if they are tailored to suit local contexts and responds to stakeholders’ needs [18]. As such, formative work was conducted to inform the design of the dissemination plan. Focus group discussions (FGDs) and interviews are established methods to effectively gain meaningful insights from, and assure involvement of, stakeholders [19, 20]. Twelve focus group discussions (FGDs) were conducted in six ECECs which involved teachers (*n* = 18) and parents (*n* = 18) of children enrolled in the respective ECECs (i.e., one FGD for each participant group in each ECEC; three participants in each FGD). Two experienced researchers facilitated the discussions which explored the participants’ (1) awareness and knowledge of the movement guidelines for young children in Hong Kong, and (2) perspectives on how these guidelines might be disseminated effectively so that adults can promote them in children. Open-ended questions were asked to initiate the discussions with participants (e.g., “what kinds of activities would help the teaching staff in your kindergarten understand the movement guidelines for children in Hong Kong?”). To mitigate the possibility of some FGD participants dominating the discussion [21], the facilitators prompted each participant to contribute any further thoughts to the discussion prior to transition of topics. Six individual interviews were conducted with stakeholder representatives (i.e., ECEC principal, ECEC program director, ECEC leadership and management expert, family psychologist, early childhood education academic, and public health academic). The interviews explored the participants’ (1) understanding of the system factors that enable and hinder healthy movement behaviors of young children in Hong Kong, and (2) perspectives on how the movement guidelines might be understood and promoted by teachers and parents in the local context.

The data gathered through the FGDs and interviews were examined using a six-phase analytic approach to thematic analysis [22]. It was determined that teachers and parents were generally aware that there are movement guidelines for young children in Hong Kong, but their knowledge of the specifications (i.e., minutes, hours), rationale, and benefits associated with these guidelines was limited. Furthermore, time constraints that affect teachers (i.e., classroom scheduling) and parents (i.e., long working hours) hinder their ability to ensure that children are meeting the movement guidelines. It was also confirmed that the socio-cultural context that currently prevails in Hong Kong puts an emphasis on early academic pursuits which are viewed as crucial to get children on a path to success. This perspective inevitably influences the learning activities in ECECs and the patterns of daily activities at home and in the wider community.

Based on the findings of the formative work, the following content will be disseminated: (1) specifications and rationale behind the movement guidelines, (2) benefits that children might have by meeting each of the guidelines, and (3) practical strategies that can be implemented daily by teachers (i.e., in class) and parents (i.e., daily activities) to promote uptake of the guidelines. Furthermore, the dissemination plan also needs to address issues that relate to: (1) teachers’ constraints due to the current curriculum expectations, (2) parents’ constraints due to competing work demands, (3) local caregiving practices such as participation of grandparents and nannies, and (4) motivation of adults to engage in healthy movement behaviors themselves.

The dissemination activities that are summarized in Table 1 will take place over 8 months of one school year (i.e. September 2021 to May 2022). Educational meetings (i.e., workshops, seminars) will be held separately for two participant groups (i.e. teachers and principals, parents and primary caregivers) in each participating ECEC. Trained project staff will conduct face-to-face sessions in the first month of the implementation; and offer subsequent sessions on a quarterly basis for reinforcement of shared ideas and concepts. These meetings will facilitate the stakeholders’ understanding of “why” (i.e. rationale) and “how” (i.e. actions) in relation to supporting children to meet the movement guidelines. A maximum of three face-to-face sessions could be conducted in each ECEC over the implementation period; the actual number would be recorded for the evaluation (see Process Evaluation section). Continuous engagement will be done through dedicated social media platforms (e.g., Facebook, WhatsApp). Informational and educational materials will be distributed to parents and teachers in multiple media (i.e. print, images, videos) over the eight-month period. Consistent with the *Kindergarten Education Curriculum Guide of Hong Kong* [23], the materials will integrate recommendations and practices with daily life activities of children in ECECs. The materials will equip the target adult recipients with a range of practicable ideas. A dedicated project staff will monitor the social media platforms, provide timely feedback, and facilitate knowledge sharing.

**Table 1 Tab1:** Activities for dissemination of the movement guidelines for young children

Participant Groups	Activity	Description
(1) teachers and principals (2) parents and primary caregivers	Educational meetings (workshop/seminar)	• Conducted on-site of the ECEC and delivered separately for the participant groups. • Introduction of the movement guidelines; included are the rationale and evidence behind the guidelines, and practical strategies that can enable children to meet the guidelines. • Content tailored according to the needs of the participant groups (e.g., lesson context for teachers). • Minimum of one meeting per participant group; ECECs may request follow-up sessions (maximum of three sessions per participant group in total).
	Social media	• Reminders through online messaging chat groups (e.g., WhatsApp) will reinforce the concepts that were introduced in the educational meetings. • Participants can ask questions/clarifications, which the project team will respond to. Chat groups will be set up separately for the participant groups in each ECEC. • Practical strategies for daily activities will be shared through Facebook and/or Instagram • Minimum of bi-weekly updates will be initiated by the project team; participants may ask questions at any time.
	Resource materials	• Printed materials (i.e., posters, brochures, activity sheets) will be made available in the ECECs for teachers and parents to take. • Multi-media such as videos and picture cards will be made available online (e.g. YouTube) and will be linked to social media updates.

### Evaluation plan

The evaluation will include a formative component to examine the implementation (i.e., process evaluation) and a summative component to examine the outcomes (i.e., outcome evaluation) [24]. The formative component will enable early resolution of barriers and enhancement of facilitators. The summative component will examine the overall implementation, and identify the factors that influenced the delivery of outcomes.

#### Recruitment

Eight ECECs, from across the three major districts of Hong Kong (i.e., Hong Kong Island, Kowloon, New Territories), will be recruited to join the implementation. The inclusion criteria for ECECs are that they: (1) are included in the published list of kindergartens by the Education Bureau, (2) follow the *Kindergarten Education Curriculum Guide of Hong Kong* [23], and (3) offer classes across three kindergarten levels (i.e., K1, K2, K3). A second group of eight ECECs, who meet the same eligibility criteria and with comparable background to the first group (i.e., ECEC size, location), will also be recruited to join a comparison group for the outcome evaluation. This second group will participate in the activities for the dissemination of the movement guidelines (i.e., educational meetings, social media, resource materials) in the school year following the implementation period. Given the constraints associated with the recruitment of ECECs to participate in projects during a pandemic, the recruitment process will be purposive. The timeline for joining the project will be the prerogative of each ECEC (i.e., hence, the group to which they will be allocated to).

#### Participants and sample size

In the formative evaluation, participants will consist of teachers (*n* = 24), administrators/ principals (*n* = 8), and parents/primary caregivers of children aged 3 to 6 years (*n* = 240) from the first group of eight ECECs (i.e., the implementation group).

In the outcome evaluation, the required sample size was calculated for the planned logistic regression analysis of the primary outcome (see Data Processing and Analysis section). It was calculated that assuming an effect size of adjusted odds ratio = 1.5, alpha at 0.05, and power at 80%, a total sample size of *N* = 242 parents/primary caregivers (and their children) is required from the two groups of ECECs (i.e., the implementation and comparison groups). With an assumed 40% non-response rate from the combined implementation and comparison groups (*N* = 480 parents) and a further 10% with incomplete data, we expect complete responses from a sample size of *N* = 240.

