The secondary outcome of knowledge and awareness of the movement guidelines by parents and teachers will be compared between the implementation and comparison groups using descriptive and inferential statistics, whilst accounting for participant characteristics (e.g., age, sex) and ECEC. Parametric statistics will be used when assumptions of normality are met. All statistical analysis procedures will be performed on SPSS 26.0 with statistical significance set at *p* < 0.05.

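### A total of 242 children cannot give 80% power at an odds ratio of 1.5 for implementation versus comparison group; before clustering, two-sided power is below 35% at any control rate

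*Protocol article*

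**What the plan says.** The section on participants and sample size states that "the required sample size was calculated for the planned logistic regression analysis of the primary outcome". It then gives the inputs and the result: "assuming an effect size of adjusted odds ratio = 1.5, alpha at 0.05, and power at 80%, a total sample size of" 242, counted over both groups together ("242 parents/primary caregivers (and their children) is required from the two groups of ECECs"). The next sentence starts from 480 parents, allows 40% for non-response and a further 10% for incomplete data, and concludes that "we expect complete responses from a sample size of" 240.

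The section on data processing and analysis describes the regression. It estimates how much the dissemination activities (implementation or comparison group), child characteristics and the centre contribute to the likelihood that a child meets each guideline component. The recruitment section plans eight centres per group.

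The sample-size text gives no control rate, sidedness or intraclass correlation. The only external rates are in the section on movement behaviours in Hong Kong. A local survey found that "less than 30% achieved the recommended 180 min of daily physical activity", and median screen time was 60 minutes. The article says that nothing is known about sleep.

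**The concern.** An odds ratio of 1.5 between two groups is a modest difference, for example 30% against 39.1%. About 121 children per group is far fewer than such a difference usually needs. The four figures (242, 1.5, 0.05 and 80%) are stated together as one calculation for one named analysis, so they can be tested against each other.

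This is the only justification of sample size for the primary outcome, and evaluating impact on children is a stated aim. The article also says that insights will be shared with the Centre for Health Protection. If the 80% figure stands, a non-significant result could be taken as evidence against an odds ratio of 1.5 when the study had little chance of detecting one.

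**Working it through.** **Inputs from the article.** Odds ratio 1.5; alpha 0.05; power 80%; total 242; binary exposure; eight centres per group.

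**Assumptions.** Equal groups (121 each); two-sided test, with one-sided also tried; control rate p0 varied, because the sample-size text gives none.

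**1. Can 242 be reproduced for two groups?** With p1 = 1.5·p0/(1 − p0 + 1.5·p0) and p̄ = (p0 + p1)/2, the total is

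N = 2·[1.96·√(2p̄(1 − p̄)) + 0.842·√(p0(1 − p0) + p1(1 − p1))]² / (p1 − p0)².

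At p0 = 0.30: p1 = 0.3913 and p̄ = 0.3457. The two square roots are 0.6726 and 0.6695, and p1 − p0 = 0.0913. So N = 2 × (1.318 + 0.563)² / 0.0913² ≈ 850.

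**2. Power with 242.** Power = Φ{[(p1 − p0)·√121 − 1.96·√(2p̄(1 − p̄))] / √(p0(1 − p0) + p1(1 − p1))}. At p0 = 0.30 this is Φ[(1.004 − 1.318)/0.6695] = Φ(−0.469) = 32%.

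| Control rate | Rate at OR 1.5 | Total N for 80% | Power at 242, two-sided | Power at 242, one-sided |
|---|---|---|---|---|
| 10% | 14.3% | 1822 | 17% | 27% |
| 20% | 27.3% | 1070 | 26% | 38% |
| 30% | 39.1% | 850 | 32% | 44% |
| 45% | 55.1% | 767 | 34.8% | 47.1% |
| 50% | 60.0% | 775 | 34.5% | 46.7% |
| 70% | 77.8% | 1000 | 28% | 39% |
| 79% | 84.9% | 1310 | 22% | 33% |

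The row at 45% is the optimum over all control rates. The one-sided minimum N is 604. No control rate brings the required number near 242.

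**3. Where might 242 come from?** The logistic formula for a continuous covariate, with the odds ratio taken per standard deviation, is N = (1.96 + 0.842)² / [p(1 − p)(ln 1.5)²]. At an event rate of 0.27 this is 7.849/(0.1971 × 0.1644) = 242.2. The rate 0.27 is back-fitted. At 0.30 the same formula gives 227, and 239 if an R² of 0.05 with the other covariates is added. With one-sided alpha it gives 235 at a rate of 0.20.

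**4. Clustering (conditional).** With 242/16 = 15.1 children per centre, the design effect is 1 + 14.1 × ICC. The article gives no ICC; 0.02 and 0.05 are assumed.

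| ICC | Design effect | Effective N | Power at 15% / 30% / 45% / 50% control rate |
|---|---|---|---|
| 0.02 | 1.28 | 189 | 18% / 26% / 28% / 28% |
| 0.05 | 1.71 | 142 | 15% / 21% / 22% / 22% |

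**5. Odds ratio detectable with 80% power, 240 complete responses** (15 per centre; design effects 1, 1.28 and 1.70).

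| Control rate | No clustering | ICC 0.02 | ICC 0.05 |
|---|---|---|---|
| 20% | 2.27 | 2.50 | 2.85 |
| 30% | 2.11 | 2.33 | 2.64 |
| 40% | 2.07 | 2.28 | 2.60 |
| 50% | 2.10 | 2.33 | 2.67 |

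**6. Losses.** Both percentages taken of 480: 480 × (1 − 0.40 − 0.10) = 240. In sequence: 480 × 0.60 × 0.90 = 259. At 259, two-sided power is still at most about 37%.

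**The case against.** The article is condensed, and a fuller document may hold the control rate, the ICC and the software inputs. That is a fair defence against a complaint of omission, but it does not meet this point. No control rate makes 242 sufficient for a binary exposure with equal groups, and any positive ICC lowers power further. Covariate adjustment does not help, because 1.5 is already the adjusted odds ratio. Even 480 complete responses, with no losses at all, would give at most 60%.

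Three stronger readings are tempting, and the article does not support them:

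- **That the power is 32%, or 20% to 26% after clustering.** The 30% is an upper bound from a survey of the 180-minute target alone, while the study's activity criterion also requires 60 minutes of vigorous activity. A median screen time of 60 minutes suggests about 50% for that component, and the article has no rate for sleep. The ICC is not in the article. The analysis does include centre in the model, although that puts no allowance into the sample size. Only the bound is free of these assumptions.
- **That the group variable was entered as continuous.** The continuous-covariate formula can give 242, but only with inputs that the article does not state, and more than one set of inputs comes close. This remains inference.
- **That the allowance for losses is wrong.** It is coherent if both percentages refer to the 480. What is left is an expected number two below the stated requirement, worth about a quarter of a percentage point of power.

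**Conclusion.** The statement is wrong as written. For the planned two-group contrast with equal groups, 242 children give less than 35% two-sided power at an odds ratio of 1.5 at every control rate, and at most 47.1% one-sided. The number needed for 80% two-sided power is at least about 767, more than three times the stated figure (767/242 ≈ 3.2).

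This rests only on the binary exposure, equal group sizes and independent children. Dependence within centres makes it worse. The size of that loss is conditional: about 15% to 28% power for control rates of 15% to 50%, if the ICC is 0.02 to 0.05. A null result should not be read as evidence against an odds ratio of 1.5.

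**What to change.** Drop the claim of 80% power at 1.5 and state what the design delivers, with the assumptions labelled. For example:

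> With about 240 complete responses, power at an odds ratio of 1.5 is below 35% (two-sided) at any control rate before allowing for clustering. The odds ratio detectable with 80% power is about 2.1 at a control rate of 30% to 50% ignoring clustering (2.3 at 20%), and about 2.3 to 2.7 at 30% to 50% if the intraclass correlation is 0.02 to 0.05 (assumed).

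If the authors hold a control rate or an ICC from another source, they should state it and use it in place of these ranges. As a minor correction in the same paragraph, say whether the 10% applies to all 480 parents (240 expected, two below 242) or to responders only (259 expected).

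The cost is one rewritten paragraph and a less favourable power statement. No extra participants or data are needed.
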